### Outcome variables

1. The primary outcome is the change of endothelium-dependent brachial artery flow-mediated dilatation (FMD) after three months of regular aerobic exercise. [Time Frame: Baseline and 32 to 36 weeks of gestation].

2. The secondary outcome is the concentration of F2-isoprostanes in umbilical cord blood of newborn [Time Frame: Delivery].

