In order to evaluate the effects of maternal regular physical exercise and micronutrients supplementation on newborn's oxidative stress (concentration of F_2_-Isoprostanes in umbilical cord blood), a comparative analysis will be executed to establish if the effects are different among study groups using analysis of covariance (ANCOVA), a form of general linear model [26]. We will include the baseline measure as a covariate in the model and pre-specified potential confounding factors: maternal age, previous physical exercise level, tobacco or alcohol consumption, differences in diet report and pregnancy complications such as hypertension and diabetes [26]. These will be included regardless of whether baseline imbalance exists. This approach has been chosen because confounder selection strategies that are based on collected data can result in models with poor statistical properties [26]. This will adjust appropriately for any baseline imbalance and will provide the most powerful analysis. Adjusted estimates of intervention effect from this model will be reported as the primary analysis in the trial publication.

Finally, we will investigate if there is an interaction between the two interventions for the primary outcome at 32 gestational weeks (regular physical exercise) or until the birth (micronutrients supplementation). For these analyses we will include appropriate interaction terms in the models [26]. The trial is not powered to detect these interactions and is likely to have poor precision for the interaction terms. We plan to report regression coefficients for the interaction terms and their 95% confidence intervals.

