### Exclusion criteria

Pregnancy with history of high blood pressure, chronic medical illnesses (cancer, renal, endocrinologic, psychiatric, neurologic, infectious and cardiovascular diseases), persistent bleeding after week 12 of gestation, poorly controlled thyroid disease, placenta praevia, incompetent cervix, polyhydramnios, oligohydramnios, history of miscarriage in the last twelve months, diseases that could interfere with participation in the study (following recommendations from ACSM 2000, ACOG 2002) [18,19] or any medical condition are excluded from the trial.

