### Baseline assessments and active follow-up

**- Visit B**: measurements of blood pressure, anthropometric parameters, FMD, functional capacity (VO_2Max_), and electrocardiogram. During this visit, the participants will be randomized to one of the four intervention groups. For this purpose, a randomization system using maximum blocks of 10 will be used.

**- Visit C**: within 32 and 36 week period of gestation, measurements described above are repeated.

**- Visit D**: the following pregnancy outcomes will be recorded at postpartum: pregnancy duration, blood pressure, characteristics of delivery (route and duration of delivery, and postpartum haemorrhage), newborn outcomes (gestational age at birth, Apgar score, weight, height, head circumference, and abdominal circumference). With these measures, the following variables will be calculated: weight/height^3^, head circumference/birth weight, and weight/height [27]. In umbilical cord blood, measurements of the following outcomes will be obtained: oxidative stress biomarker (F_2_-isoprostanes). In addition, the number of prenatal controls and information regarding pregnancy complications will be registered.

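### The adjusted model must include pregnancy hypertension and diabetes, which in this trial arise almost entirely after randomisation, so its estimate is open to bias and does not target the total effect of assignment

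*Protocol article*

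**What the plan says.** In the protocol article, the Analytic plan introduces an ANCOVA for newborn oxidative stress. Its covariates are the baseline measure and a set of pre-specified potential confounders: maternal age, earlier exercise level, tobacco or alcohol use, and "differences in diet report and pregnancy complications such as hypertension and diabetes". Inclusion is mandatory: "These will be included regardless of whether baseline imbalance exists". The article adds that the model will deal properly with imbalance at baseline, and then states: "Adjusted estimates of intervention effect from this model will be reported as the primary analysis in the trial publication".

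The outcome for which this model is introduced is the secondary one: "The secondary outcome is the concentration of F2-isoprostanes in umbilical cord blood of newborn [Time Frame: Delivery". The primary outcome is different: "The primary outcome is the change of endothelium-dependent brachial artery flow-mediated dilatation (FMD) after three months of regular aerobic exercise". For that outcome the same section names one-way ANOVA or Kruskal-Wallis, followed by GEE, and lists no complication covariates.

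Three other places bear on timing. Exclusion criteria begins "Pregnancy with history of high blood pressure, chronic medical illnesses (cancer, renal, endocrinologic, psychiatric, neurologic, infectious and cardiovascular diseases" and ends with a catch-all for other medical conditions. Inclusion Criteria asks for a normal pregnancy at 16 to 20 weeks in nulliparous women. Baseline assessments and active follow-up places randomisation at Visit B and says of postpartum Visit D that "information regarding pregnancy complications will be registered".

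**The concern.** A confounder of a treatment comparison has to precede assignment. In a randomised trial, an event that occurs afterwards cannot have influenced assignment, but assignment can influence it. Adjusting for such an event can do two things. It removes whatever part of the effect runs through the event. If the event and the outcome share an unmeasured cause, it also creates an association between arm and outcome that is not causal.

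At stake is what the reported estimate means. The Analytic plan attributes all change in outcome to the assigned treatment, which is a total effect. A coefficient conditional on hypertension and diabetes that develop during follow-up is a different quantity, yet the article gives it the status of primary analysis.

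**Working it through.** **Step 1. When the covariates arise.**
- Eligibility and Inclusion Criteria: nulliparous women without need of specialised care, with a normal pregnancy at 16 to 20 weeks. An earlier delivered pregnancy is therefore not a source of these complications.
- Exclusion criteria: prior high blood pressure and chronic endocrine or cardiovascular disease are excluded.
- Randomisation takes place at Visit B. The Sample size section puts that visit at weeks 12 to 20, so randomisation is at week 20 at the latest.
- Complications are registered at Visit D, after delivery.

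If eligibility is applied, hypertension and diabetes are close to absent at randomisation. Read as baseline variables, they would be nearly constant and useless as covariates. Read as they will be recorded, they are post-randomisation events. Neither reading lets them correct a baseline imbalance.

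**Step 2. Whether the interventions could affect them.** The Background says that both interventions have been reported to raise nitric oxide synthesis, and ties this to endothelial function and lower oxidative stress. On that rationale an effect on hypertensive complications is plausible. The article offers no comparable route for diabetes.

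**Step 3. Size, under assumptions.** The article gives no complication rate, no effect of treatment on complications and no effect of complications on F2-isoprostanes. There is no figure to reproduce, and every input below is assumed: residual SD 1 and a direct treatment effect of −0.30.

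Let p0 and p1 be the complication risks without and with the intervention, and g the effect of a complication on the outcome. With no shared cause:
- total effect = −0.30 + g × (p1 − p0)
- effect adjusted for complications = −0.30
- attenuation = 1 − adjusted/total

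| p0 | p1 | g | Total | Adjusted | Attenuation |
|---|---|---|---|---|---|
| 0.15 | 0.15 | 0.8 | −0.300 | −0.300 | 0% |
| 0.15 | 0.10 | 0.5 | −0.30 − 0.025 = −0.325 | −0.300 | 0.025/0.325 = 8% |
| 0.15 | 0.075 | 1.0 | −0.30 − 0.075 = −0.375 | −0.300 | 0.075/0.375 = 20% |
| 0.20 | 0.10 | 1.0 | −0.30 − 0.100 = −0.400 | −0.300 | 0.100/0.400 = 25% |

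Next, add an unmeasured standard normal cause of both complication (log-odds coefficient 1) and outcome (coefficient 0.5). Here p0 and p1 are the risks at the average value of that cause. The results come from simulation with 2 million women per scenario:

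| p0 | p1 | g | Total | Adjusted | Attenuation |
|---|---|---|---|---|---|
| 0.15 | 0.15 | 0.8 | −0.302 | −0.300 | about 0% |
| 0.15 | 0.075 | 1.0 | −0.383 | −0.261 | 32% |
| 0.20 | 0.10 | 1.0 | −0.401 | −0.251 | 38% |
| 0.20 | 0.10 | 0 | −0.300 | −0.254 | 15% |

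In the last row the complication has no effect on the outcome, so the whole 15% comes from the shared cause. A second set of assumptions (control risk 11% to 16%, odds ratio 0.5 to 0.7, g from 0.5 to 1.0, shared cause with coefficient 0.5) ran from −0.316 against −0.294 (0.022/0.316 = 7%) to 24%. Together the scenarios with lower risk under intervention span about 7% to 38%.

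**Step 4. If the model were also used for FMD.** FMD is measured at 32 to 36 weeks, while complications are recorded after delivery. Some of them could then occur after the outcome they are meant to explain.

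**The case against.** A reader might infer that the trial's headline effect is biased. The documents do not show that. Bias for the total effect requires an intervention to change complication risk; with equal risks the adjusted and total effects agree, with or without a shared cause. This objection stands, so the estimate can only be called open to bias.

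A reader might also infer that the FMD analysis is affected. That is not established, because FMD is assigned to other methods. The text is ambiguous: the ANCOVA is said to include a baseline measure, which cord blood cannot supply, and to provide the primary analysis. F2-isoprostanes are the only outcome clearly covered.

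It is tempting to say that the plan breaks intention-to-treat. The article describes that principle as analysis by original allocation, keeping non-compliant women and those with missing outcomes, and a covariate violates neither part. The conflict is with the narrower statement that all outcome change is credited to assigned treatment.

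The diet report might be suspected in the same way, but its timing is not stated, nor is that of tobacco and alcohol use. The point does not rest on them.

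Finally, the shift may be modest against sampling error. With 160 women against 160 and SD 1, the standard error is √(2/160) = 0.11. Shifts of 0.02 to 0.15, as in the scenarios above, are about 0.2 to 1.4 standard errors, towards the null. That tempers the urgency, but it does not make these covariates confounders.

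**Conclusion.** The point holds in a limited form. The ANCOVA introduced for cord-blood F2-isoprostanes, and described as the publication's primary analysis, must adjust for conditions that the trial's own eligibility rules and visit schedule place almost entirely after randomisation. They cannot do the job of baseline adjustment given to them, and the resulting estimate does not target the total effect of assignment.

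Whether it is biased, and by how much, cannot be derived from the article. The bias is zero if complication risk is the same across arms. The 7% to 38% attenuation depends wholly on assumed rates and effects and is no prediction. The conclusion about timing rests on eligibility being applied as written. The plausibility of an intervention effect rests on the Background's own rationale, and only for hypertensive complications.

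**What to change.** Remove pregnancy complications from the adjusted model. Keep the baseline value of the outcome where one exists, maternal age, previous exercise level, and tobacco or alcohol use and diet report as recorded at baseline, and say that these are the pre-randomisation values. State which outcome or outcomes the model serves. Report hypertension, diabetes and other complications by arm as outcomes. If a model containing them is still wanted, label it exploratory.

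The cost is one or two sentences in the Analytic plan. No extra data, visits or participants are needed, because complications are already to be registered at Visit D.

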### Eligibility

Pregnant nulliparous women (n = 320) in a range of age between 16 to 30 years will be invited to participate in this randomized clinical trial. These women will not any indications of additional specialized care.

### Exclusion criteria

Pregnancy with history of high blood pressure, chronic medical illnesses (cancer, renal, endocrinologic, psychiatric, neurologic, infectious and cardiovascular diseases), persistent bleeding after week 12 of gestation, poorly controlled thyroid disease, placenta praevia, incompetent cervix, polyhydramnios, oligohydramnios, history of miscarriage in the last twelve months, diseases that could interfere with participation in the study (following recommendations from ACSM 2000, ACOG 2002) [18,19] or any medical condition are excluded from the trial.

### Inclusion Criteria

Nulliparous women not involved in a structured exercise program during pregnancy will be chosen, having a live fetus at the routine ultrasound scan, and a normal pregnancy, with gestational age 16 to 20 weeks. Written informed consent will be obtained from each woman prior to the inclusion in the study.

### Blinding and Randomization methods

The randomization procedure into the two study arms was performed by the Fundación FES Social, Division de Salud, Cali-Colombia (Biometry and Epidemiology Department). The biometricians compiled an allocation list which was the basis for the pharmacists to prepare sequentially numbered envelopes containing two boxes of study medication for trial use. The boxes contained a zinc (30 mg), selenium (70 μg), vitamin A (400 μg), alphatocopherol (30 mg), vitamin C (200 mg), and niacin (100 mg) or an equivalent placebo capsule (maltodextrine). After inclusion into the trial, the study researcher assigned the content of the lowest numbered envelope to the participant. The principal investigator and coordinator the allocation sequence, and randomization is performed through a secure website which ensures allocation concealment. All participants and study personnel (including investigators, research coordinators, data analysts) will be blinded to treatment allocation throughout the trial (Table 1). Access to the allocation code will be restricted to one study statistician who will not perform the final study analyses. Also, neither the participant nor the study researcher knew about the content of the boxes, the capsule was not distinguishable. Since no specific qualifications or experience are required for the research assistants, training will be provided prior to the initiation of the trial about protocol and measurement procedures and methods used to maintain the blindness. These procedures are also detailed in the study operations manual. Moreover, the importance of maintaining the blinding and allocation concealment will be reinforced by regularly scheduled conference calls at the sites and daily meetings with the field investigators, Figure 1.

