**Methods and design:**

320 pregnant women attending to usual prenatal care in Cali, Colombia will be included in a factorial randomized controlled trial. Women will be assigned to the following intervention groups: *1. Control group: *usual prenatal care (PC) and placebo (maltodextrine). *2. Exercise group: *PC, placebo and aerobic physical exercise. *3. Micronutrients group: *PC and a micronutrients capsule consisting of zinc (30 mg), selenium (70 μg), vitamin A (400 μg), alphatocopherol (30 mg), vitamin C (200 mg), and niacin (100 mg)*. 4. Combined interventions Group: *PC, supplementation of micronutrients, and aerobic physical exercise. Anthropometric measures will be taken at the start and at the end of the interventions.

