## Methods/Design

### Study Design

This is a single blind, randomized controlled 2 × 2 factorial trial designed to evaluate the effectiveness of micronutrients supplementation and regular aerobic exercise during pregnancy. This design provides the advantage of assessing the independent and cumulative effects of the interventions in nulliparous pregnant women.

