#### 2. Exercise Group

Regular aerobic exercise: walking (10 minutes), aerobic exercise (30 minutes), stretching (10 minutes), and relaxation exercises (10 minutes) during a three-month period. Exercise will be performed during 3 sessions per week. A physical therapist and a physical educator will supervise all sessions. The exercise-program is according to the American College of Obstetrics and Gynecology (ACOG) [18] and the American College of Sports Medicine (ACSM) exercise prescription [19]. Aerobic activities will be performed at moderate intensity (60-70% of maximal heart rate) measured by the 6-20 Borg's rating scale (PER). Each session will start with a 5 min warm up, followed by 30 min of aerobic activity, including a 5 min cool down. Subsequently, a 15 min strength training for upper limbs, lower limbs, and deep abdominal muscle stabilization. The last 5 min consist of stretching and relaxation exercises. (Table 1)

**Table 1 T1:** Pregnancy 2 X 2 Factorial Design

	Regular Physical Exercise	
	
	-	+

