**Micronutrients**		
-	Usual Prenatal Care + Placebo	Usual Prenatal Care + Regular physical exercise
+	Usual Prenatal Care + Micronutrients Supplementation	Usual Prenatal Care + Regular physical exercise + Micronutrients Supplementation

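### The claim that all participants and staff are blinded cannot hold for supervised exercise; masking should be stated by factor and role, and the placebo entry in Table 1 reconciled

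*Protocol article*

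**What the plan says.** **On blinding.** The Blinding and Randomization methods section says "All participants and study personnel (including investigators, research coordinators, data analysts) will be blinded to treatment allocation throughout the trial" and ends that sentence with a pointer to Table 1, the 2 × 2 layout. The Study Design section says "This is a single blind, randomized controlled" and does not say which party is blind.

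**On exercise delivery.** The Exercise Group section says "Exercise will be performed during 3 sessions per week" over a three-month period, and "A physical therapist and a physical educator will supervise all sessions". The Control Group section gives usual prenatal care and placebo. It adds that the national guidelines include neither exercise prescription in pregnancy nor counselling by a physical therapist. No sham or attention control is described for any arm.

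**On masking devices.** The Blinding section describes numbered envelopes, boxes holding micronutrients or an equivalent placebo, and capsules that cannot be told apart. It limits access to the allocation code to one statistician who will not do the final analyses. The FMD section has recorded images measured by two blinded observers.

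**On placebo in the exercise-only arm.** The abstract gives that arm "PC, placebo and aerobic physical exercise". In Table 1 the cell reads "Usual Prenatal Care + Regular physical exercise", while the neighbouring control cell in the same row names placebo.

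**The concern.** In a factorial trial, blinding belongs to each factor separately. Here one factor is a capsule with a matched placebo and the other is a visible, supervised activity. One sentence covering everyone and every allocation claims a protection for the exercise contrast that the design cannot give. A reader of the results would then give the exercise estimate the credibility of a masked comparison. The primary outcome is itself worded around three months of exercise, so this is not a side contrast.

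The blanket sentence also hides what a reader needs to know, namely which roles really are masked. The FMD section is specific about the two image readers but silent about the person who acquires the images. For that role the only assurance is a sentence already known to be wrong for other roles.

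The placebo discrepancy matters because masking of the micronutrient factor depends on women without micronutrients taking a capsule whether or not they exercise.

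**Working it through.** There is no sample size, power or alpha figure to reproduce for this point. The check is a comparison of sections, plus a count of the women affected.

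**1. Does the blinding sentence cover exercise?** It refers to treatment allocation and cites Table 1, whose columns are exercise absent and present. On its face it covers both factors.

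**2. Can it be true for exercise?**

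| Role | What the article says | Masked to exercise? |
|---|---|---|
| Participant | Attends three sessions a week, or none; no sham | No |
| Physical therapist, physical educator | Supervise every session | No |
| FMD image readers | Two observers, described as blinded | Yes, as stated |
| Data analysts | Named as blinded; code held by a statistician who does not do the final analyses | Possible, as stated |
| FMD image acquisition, GC-MS laboratory | Covered only by the blanket sentence | Not stated specifically |

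The first two rows are enough to make the sentence false.

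**3. Does it agree with the design label?** Single blind and a list covering participants, investigators, coordinators and analysts do not describe the same trial.

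**4. What does the described masking cover?** Envelopes, boxes and matched capsules mask the capsule only. The same section speaks of two study arms, whereas Visit B randomizes to four groups. This suggests that the section was written for the capsule comparison and not adapted to the factorial.

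**5. Size for exercise.** The Sample size section gives 80 per group. The exercise contrast is (80 + 80) against (80 + 80), that is 160 against 160. All 320 women know their exercise status.

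**6. Size for the capsule, if Table 1 were literal.**
- Exercise half: 80 women with no capsule against 80 with one. Micronutrient status is evident for 80 + 80 = 160 women, and 160/320 = 50%.
- No-exercise half: 80 on placebo against 80 on active. This stays masked.

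If the abstract is followed instead, both halves stay masked.

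**The case against.** **The sentence may mean the capsule only.** The surrounding text is about boxes and capsules, so this reading is possible. The pointer to Table 1 works against it, and the sentence does not say so. If that is the intention, saying so is the correction needed.

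**Single blind may mean assessor-blind.** That would fit the blinded image readers. It still does not match the list in the Blinding section, and the label does not say who is blind.

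**The operations manual may hold the detail.** The article says that blinding procedures are set out there, and role-level detail could be. A manual cannot make the published sentence true.

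**The declared outcomes are objective.** This stands. FMD is read by blinded observers and cord-blood F2-isoprostanes are measured by GC-MS. A reader might infer that open exercise allocation biases self-reported outcomes. The physical activity, diet and quality-of-life questionnaires are not listed under Outcome variables, so that inference is not supported. Changes in behaviour between visits remain a possible route to bias, but the article gives no figure from which to size it.

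**Placebo probably does go to the exercise-only arm.** This largely stands. A reader of Table 1 might infer that these women receive no capsule, and that the micronutrient contrast is therefore unblinded. The article does not support this. The abstract lists placebo for them, and the envelope procedure gives every included woman a box of active or placebo capsules, with no exception for exercisers. The silence of the Exercise Group section is weak evidence, because that section also omits prenatal care, which all women receive. Even a literal Table 1 would unmask only the exercise half.

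**Conclusion.** The point holds as a false statement about blinding and an internal inconsistency. It is not a flaw in the choice of design, since open allocation cannot be avoided for supervised exercise. The exercise contrast is open to all 320 women and to those who run the sessions. It should be read as open-label with masked outcome reading.

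The placebo discrepancy is secondary: a contradiction to reconcile, not evidence that one arm goes without a capsule. Its worst case is loss of masking in 80 against 80 women, half of the micronutrient contrast.

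The counts rest on the planned 80 per group. The conclusion also assumes that no sham or attention control exists beyond what the article describes. The correction should be made because it changes what the trial can claim about exercise. The blinded FMD reading and the laboratory assay limit the likely effect on the two declared outcomes.

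**What to change.** Replace the blanket sentence and the bare single-blind label with one statement by factor and role:

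- Capsule allocation: masked to participants and staff.
- Exercise allocation: open to participants and supervising staff.
- FMD image readers and data analysts: masked to both factors.
- FMD sonographer and laboratory: also kept masked to both where feasible, which only keeps what the Blinding section already promises.

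State that the exercise contrast will be interpreted as open-label with masked outcome reading. Correct the reference to two study arms in the same edit.

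Reconcile Table 1, the abstract and the envelope procedure, so that both cells without micronutrients are described consistently and in line with what is actually dispensed.

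The cost is mostly wording. The one practical element is keeping the sonographer and laboratory masked, for example by asking women not to reveal their group at the FMD visit; the sites should confirm that this is workable. Sample size, outcomes and models stay as they are.
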